### Participant timeline {18}

Table 1 depicts the participation timeline, detailing the time points of instruments’ administration. In a pre-treatment assessment (T0p), primary and secondary outcome measures are readministered at the start of treatment in order to minimise variance in time between pre- and post-treatment measurements and account for the effect of extensive waiting list duration. Questionnaires are readministered if, due to the waiting list, ten weeks or more pass after baseline (T0b). However, the STiP-5.1 interview is readministered if 6 months have expired after baseline before the start of treatment. Participants are followed up at 3 (T1), 6 (T2), 12 (T3), 18 (T4; post-treatment), 24 (T5) and 30 months (T6).

**Table 1 Tab1:**
[figure not shown]
Participant timeline for the Standard Protocol Items; Recommendations for Intervention Trials (SPIRIT) {18}

### Sample size {19}

The required sample size was determined using a computer simulation. Twenty-one thousand datasets with varying sample sizes were simulated for an RCT design with seven repeated measurements on a continuous outcome variable, where both interventions exhibit equal improvement over time. The outcome measures were assumed to follow a multivariate normal distribution in both groups, with a repeated measures correlation of 0.50 and a decrease of *d* = 0.30 in both groups across the seven repeated measurements. Each of these datasets was analysed using a longitudinal multilevel model (see *Statistical methods for primary and secondary outcomes, including harms {27a}).* Subsequently, in each dataset, it was tested whether generalist treatment is non-inferior to specialist treatment by examining whether the lower limit of the two-sided 95% confidence interval of the difference between treatments in improvement over time is greater than the non-inferiority limit of *d* = 0.25. It was found that with this design, 316 participants are necessary (158 per group) to test non-inferiority with a power of 0.80 and α = 0.025. To account for attrition, which we estimate at 11.7% for the primary endpoint (T4) based on a similar study [19], the complete sample needs to consist of (316/0.883 = 357.87) 358 participants. This comes down to 179 participants per treatment condition.

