### Objectives {10}

#### Primary objective

The primary objective is to determine whether generalist treatment (GIT-PD) is non-inferior (*d* ≥ − 0.25) to specialist treatment (MBT/ST) in improving personality functioning in participants with severe personality disorders from baseline to the end of treatment (18 months; T4). In setting the non-inferiority margin, scarce evidence is available on the difference between the selected specialist treatments (MBT/ST) and no treatment [14]. However, Cristea et al. [10] demonstrated that psychotherapy is between *d =* 0.25 and *d =* 0.56 more effective than treatment-as-usual in improving BPD-relevant outcomes. Therefore, taking the statistically conservative route, the non-inferiority margin is set at *d =* − 0.25, implying that non-inferiority will be concluded if the lower bound of the confidence interval for the effect of generalist treatment relative to specialist treatment in improving personality functioning at T4 is greater than − 0.25 (Cohen’s *d*).

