### Statistical methods

#### Statistical methods for primary and secondary outcomes including harms {27a}

*Non-inferiority.* The primary research question is answered through longitudinal multilevel modelling of the short-term difference (T4; 18 months) between generalist (GIT-PD) and specialist treatment (MBT/ST) in improvement of personality functioning, following the intention-to-treat principle. Two separate multilevel mixed-effects models are used for the two primary outcomes, meaning both the STiP-5.1 at two time points and the LPFS-BF 2.0 at five time points. The model levels refer to the repeated measurements (level 1) of each individual (level 2) nested within treatment sites (level 3). Both models will be adjusted for the respective baseline outcome value, while random intercepts and slopes are modelled to account for the heterogeneous individual change trajectories over time. Furthermore, random intercepts and slopes are modelled on the treatment site level to account for heterogeneous change trajectories across sites. No further covariates will be added. Two-tailed significance levels are set at *α* = 0.05, while effect estimates are reported with corresponding 95% two-sided confidence intervals. If the required sample size is not achieved due to problems with enrolment and inclusion, all non-inferiority analyses are converted to a one-sided confidence interval approach in order to retain sufficient statistical power. In case of convergence issues, the model’s complexity will be reduced by 1) not modelling the random slope but only the random intercept at the third level of treatment site, 2) replacing treatment site with institution with regards to the third level along with the respective random intercepts and slopes, or 3) omitting the third level in the analysis altogether if necessary. Trial-level non-inferiority will be assessed using a fixed-sequence testing procedure [117], prioritising the clinician-rated LPF (STiP-5.1) due to its blinded assessment and superior capability of measuring latent PD severity [58, 59]. If non-inferiority is demonstrated on the STiP-5.1, the self-reported LPFS-BF 2.0 will be tested subsequently to provide additional supportive evidence, given its high sensitivity to change [60]. If non-inferiority is not demonstrated on the STiP-5.1, the LPFS-BF 2.0 will not be formally tested as a primary outcome, and non-inferiority cannot be concluded at the trial level. This hierarchical approach preserves statistical power while controlling the family-wise error rate across multiple endpoints and prioritising blinded assessment to minimise potential bias.

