
To answer the secondary research questions regarding long-term (T6; 30 months) non-inferiority of generalist (GIT-PD) versus specialist treatment (MBT/ST) in improving personality functioning, an identical intention-to-treat longitudinal multilevel model will be fit as for the primary outcome, while including all available repeated measures. This ultimately results in the inclusion of three and seven repeated measures for the STiP-5.1 and LPFS-BF 2.0, respectively. Likewise, to assess the short-term (T4; 18 months), as well as the long-term (T6; 30 months) non-inferiority of generalist (GIT-PD) versus specialist treatment (MBT/ST) in improving symptom severity and psychosocial functioning, the same intention-to-treat longitudinal multilevel model will be applied for each of the secondary study parameters (SIPP-SF, SCID-5-PQ, BSI, C-SSRS, WHODAS 2.0, EQ-5D-5 L, Q-LES-Q-SF). Likewise, for the short-term outcome, the five repeated measures (level 1) of each individual (level 2) are nested within treatment sites (level 3). Models are adjusted for the respective outcome’s baseline value, random intercepts, and slopes are modelled at the second and third level to account for heterogeneous individual and treatment site change trajectories over time, and two-tailed significance levels are set at *α* = 0.05, while effect estimates are reported with corresponding 95% two-sided confidence intervals. The non-inferiority margin is set at *d* = − 0.25. On top of that, all AEs and SAEs are descriptively reported for both treatment arms.

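### The stated power of 0.80 comes from a seven-measurement simulation; the deciding STiP-5.1 test has two measurements and about 0.73 power on the plan's own assumptions

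*Protocol article*

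**What the plan says.** Under Sample size {19}, the protocol article states: "Twenty-one thousand datasets with varying sample sizes were simulated for an RCT design with seven repeated measurements on a continuous outcome variable", with the same improvement assumed in both arms. The simulated outcomes are multivariate normal, "with a repeated measures correlation of 0.50 and a decrease of" *d* = 0.30 in both groups. The criterion is whether the "lower limit of the two-sided 95% confidence interval of the difference between treatments in improvement over time is greater than the non-inferiority limit". The result is that "316 participants are necessary (158 per group) to test non-inferiority with a power of 0.80 and α = 0.025". Attrition of 11.7% at T4 raises this to 358.

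Under Statistical methods {27a}, the two primary models are specified differently, "meaning both the STiP-5.1 at two time points and the LPFS-BF 2.0 at five time points". Both are adjusted for the baseline value of the outcome, with T4 (18 months) as the primary endpoint. Testing follows a fixed sequence that starts with STiP-5.1. If STiP-5.1 misses, LPFS-BF 2.0 is not formally tested as a primary outcome and non-inferiority cannot be concluded for the trial.

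The secondary 30-month models have "three and seven repeated measures for the STiP-5.1 and LPFS-BF 2.0, respectively". So, of the two primary instruments, only LPFS-BF 2.0 is ever analysed with seven measurements, and only in a secondary analysis. STiP-5.1 never is.

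**The concern.** Intermediate measurements add information about a treatment difference in change over time. A simulation with seven of them therefore says little about a test with one baseline and one post-baseline value. The sample size section points to {27a} for the model it simulated, so the mismatch lies between a section and its own cross-reference; it is not a detail left to an unseen document.

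What is at stake is the chance that the trial reaches its main conclusion. STiP-5.1 is the gatekeeper, so its power is the ceiling on the power of the trial-level claim. Funders, ethics committees and readers who see 0.80 will take it to be the power of that test.

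**Working it through.** **Inputs from the documents.** Correlation r = 0.50, true difference 0, one-sided α = 0.025, 158 evaluable per arm, attrition 11.7% (Sample size); margin 0.25 SD (Primary objective); STiP-5.1 at two time points and baseline adjustment (Statistical methods {27a}).

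**Assumptions added.** Compound symmetry, *d* scaled to a common SD of 1, and no site-level variance.

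**Formulas.** Let V be the per-person variance of the contrast in SD² units. Then SE = √(2V/n), power = Φ(0.25/SE − 1.96), and n per arm for power 0.80 = 2V(1.96 + 0.8416)²/0.25².

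**1. The plan's own figure.**
- Seven equally spaced occasions, linear time, no baseline adjustment: V = 6²(1 − 0.50)/28 = 0.643. This gives 162 per arm, N = 324, and power 0.79 at 158 per arm.
- The same model at the actual visit months (0 to 30): V = 0.597, N = 302, power 0.82.
- Attrition: 316/0.883 = 357.87, so 358, as stated.

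The stated 316 lies between the two seven-occasion results and is plausible for the design described.

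**2. The gatekeeping test.** STiP-5.1 at T0 and T4, baseline-adjusted:
- V = 1 − r² = 1 − 0.25 = 0.75
- SE = √(1.5/158) = 0.0974
- 0.25/0.0974 = 2.566
- power = Φ(2.566 − 1.960) = Φ(0.606) = 0.728

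A simulation of 20,000 trials gives 0.726. With no attrition at all (179 per arm), power would be 0.78, still short of 0.80.

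**3. Size needed for 0.80.** n = 2 × 0.75 × 7.849/0.0625 = 188.4, so 189 per arm, or 378 evaluable. 378/0.883 = 428.09, so 429 randomised.

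**4. Dependence on the correlation** (158 per arm, V = 1 − r²):

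| r | V | Power |
|---|---|---|
| 0.4 | 0.84 | 0.68 |
| 0.5 | 0.75 | 0.73 |
| 0.6 | 0.64 | 0.79 |
| 0.7 | 0.51 | 0.88 |

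Power 0.80 is reached at r of about 0.61.

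**5. LPFS-BF 2.0, for comparison.** Given baseline, each post-baseline value has variance 0.75 and each pair has covariance 0.25. The table shows the linear-time difference at the last visit, using the actual visit months.

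| Model | V | N for 0.80 | Power at 158 per arm |
|---|---|---|---|
| Five visits to T4, baseline as covariate | 0.631 | 318 | 0.80 |
| Five visits to T4, shared baseline mean | 0.624 | 314 | 0.80 |
| Seven visits to T6, baseline as covariate | 0.525 | 264 | 0.87 |
| Seven visits to T6, shared baseline mean | 0.496 | 250 | 0.88 |

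With time as categories, the five-visit T4 contrast has V = 0.75 and power 0.73, the same as STiP-5.1.

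**The case against.** The strongest reply is that the shortfall rests on one planning value. The documents report no correlation for STiP-5.1, and at r of about 0.61 the two-point test would have 0.80. That is fair as a limit on the claim: the trial's true power is not known. But the plan fixes 0.50 and gives no reason for a higher value, and it says itself that little is known about how STiP-5.1 responds to change. Leaving out site variance does not favour the concern, since the planned random site slopes would if anything lower power. The fallback to a one-sided interval applies only if recruitment falls short, so it gives no relief at full enrolment.

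Four stronger readings are tempting, and the documents do not support them.

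- A reader might infer that power is as low as 0.60 and that 504 evaluable (571 randomised) are needed. Those figures belong to an unadjusted change score (V = 2(1 − r) = 1.0). The outcome is worded as a difference in change, but {27a} plans baseline adjustment.
- A reader might infer that 0.80 fits neither primary test. An unadjusted five-visit slope does give only 0.70 to 0.71. The planned model is adjusted for baseline, and with linear time it gives about 0.80.
- A reader might take the closeness of 324 and 302 to 316 as proof of which model was run. The baseline-adjusted five-visit models give 314 and 318, which are closer. It is the wording of the sample size section that establishes seven measurements, not the arithmetic.
- A reader might relabel 0.80 as the power of the 30-month LPFS-BF 2.0 analysis. Adjusted for baseline as planned, that analysis has 0.87 to 0.88.

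The sample size section also prints the limit as 0.25 without a minus sign, where the objectives and {27a} have −0.25. This is a slip: under true equality, a lower limit above +0.25 could not occur with probability 0.80.

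**Conclusion.** The point stands for STiP-5.1. The stated power was not derived for the test that decides the trial. On the plan's own inputs that test has power of about 0.73, roughly seven points below the 0.80 presented. Put the other way, the chance of missing a true equivalence at the first step is about 27% rather than 20%.

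This rests on r = 0.50, a margin of 0.25 SD, one-sided 0.025, no true difference, 158 evaluable per arm, compound symmetry, no site variance, and reading the two-point model as a baseline-adjusted comparison at T4. The range is 0.68 to 0.88 for r from 0.4 to 0.7. The trial is not shown to be unworkable, and no comparable shortfall is established for LPFS-BF 2.0 if time is modelled as linear.

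**What to change.** Keep N = 358 and revise Sample size {19}:

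1. Rerun the simulation with the actual STiP-5.1 primary model: T0 and T4, baseline-adjusted, site level as planned, 11.7% attrition. State that power, with its range over the correlation (about 0.73 at r = 0.50 before site variance is included).
2. Describe 0.80 only as the result of the seven-measurement simulation as run. It should not be presented as the power of the STiP-5.1 test, nor as that of the baseline-adjusted 30-month LPFS-BF 2.0 analysis.
3. Report the five-measurement LPFS-BF 2.0 power separately, from its own planned model, and say how time enters: about 0.80 with linear time and baseline adjustment.
4. As an editorial correction, give the limit as −0.25.

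The cost is one simulation rerun and a reworded paragraph. It needs no outcome data and no extra participants, and can be done while enrolment continues. The downside is a less favourable stated power. For scale, 0.80 on STiP-5.1 at r = 0.50 would take 429 − 358 = 71 more randomised participants, which this point does not ask for.

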### Recruitment {20}

Within each institution, all patients assessed for intake during the recruitment period appearing eligible for study participation are asked permission by the clinician to be contacted by the research team. Research staff contacts and informs the client to further discuss participation in the trial and screen for eligibility. Strategies per site vary to the extent that at Arkin NPI, the LPF, according to the STiP-5.1, is determined after intake by research staff, while all other sites implemented the STiP-5.1 into the primary intake procedure, where it is administered by trained clinicians. Treatment sites are expected to recruit varying numbers of eligible participants based on recruitment start dates, annual intake numbers, team size, and intervention capacity. Recruitment is projected to be completed by the end of 2026. A monthly inclusion forecast per site was established at the start of recruitment and will be monitored continuously. If recruitment rates fall short, corrective actions will be implemented based on site-specific factors.

## Methods: assignment of interventions

### Sequence generation

#### Roles and tools of sequence generation {21a}

Ensured concealed sequence generation and randomisation are performed through the fully automated web-based electronic data capture system of CASTOR EDC by the two unblinded junior researchers.

#### Method of sequence generation {21b}

Participants will be randomised to either the experimental or comparator condition with a 1:1 allocation. Block randomisation, with varying block sizes of 4, 6, and 8 subjects, is stratified per participating mental healthcare institution.

### Allocation concealment mechanism {22}

The block size and randomisation sequence are randomly and automatically selected. This is an ensured concealed process, as CASTOR EDC does not release the generated randomisation code. On top of that, randomisation can only be performed by the junior researchers and the outcome remains concealed to all blinded research assistants, ensuring allocation concealment.

### Implementation {23}

Participants who meet the inclusion criteria and give informed consent are added to CASTOR EDC by the research assistants. Here, participants have their own file where all outcomes are logged. All participants are randomised in CASTOR EDC after completion of the baseline measurements. CASTOR EDC does not release the generated randomisation code, ensuring that research assistants involved in enrolment and junior researchers responsible for executing treatment allocation are blind to the future order of assignments.

### Blinding

#### Who will be blinded {24a}

Treatment providers and participants cannot be blinded due to the nature of the interventions, e.g. containing psychoeducation directly related to and explained within the framework of the intervention, leading to automatic unblinding of participants. Understandably, therapists are unequivocally aware of the intervention type they are applying. Appointments for the STiP-5.1 outcome assessments will be scheduled by unblinded research staff members for blinded research staff. Participants are asked not to disclose their allocation during the appointment. Thus, staff members administering the interview at post-treatment and follow-up timepoints will be blinded. This is further ensured through CASTOR EDC roles and permissions functions.

When data is exported from CASTOR EDC, an unblinded data manager will pseudonymise the conditions. Afterwards, the data is processed, analysed, and interpreted by blinded data managers, statisticians, junior researchers, and conclusion makers. The pseudonymisation of the data will only be undone after conclusions are drafted. In this way, statisticians and conclusion makers are ensured to be blinded. The junior researchers are not blinded during data collection to enable effective day-to-day management of the trial.

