### Data Management {26}

All study data is centrally managed and securely stored for the duration of the trial in CASTOR EDC and for 15 years after trial completion. All data in CASTOR EDC is pseudonymised and stored on EU servers based in the Netherlands [116]. Hosting is NEN7510 compliant. Multi-factor authentication for research staff is enforced. Indefinite long-term storage on secured servers is facilitated by Tilburg University through TiU Dataverse, which is based on the Harvard University Dataverse repository.

Regarding data entry, included participants receive a study ID generated by CASTOR EDC. In all data files and during statistical analysis, participants are identified through their study ID, which can only be linked to personal data through a linking file (see *Confidentiality {33}*). All interview scores and data from electronic patient file records are entered manually by research assistants, while questionnaire responses are automatically captured during administration to participants in CASTOR EDC. When possible, data entry is checked and validated for a random case sample of entered STiP-5.1 and DART scores. Missing data during entry of questionnaires is prevented by CASTOR EDC through enforced item-based validation. Completed questionnaire packages are locked and cannot be altered. Only the junior researchers and the data manager are permitted to export data. Only the necessary research staff have access to exported data files. Exported data is checked, transformed and made anonymous on secured internal servers of Arkin GGZ, and stored and analysed on secured internal servers of Tilburg University. Data transformation is executed following automated scripts to guarantee transparency and replicability. In addition, CASTOR EDC produces a complete audit trail of all actions performed, e.g. fields updated and data exported.

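### The junior researchers who carry out all randomisation cannot be counted as blinded analysts and interpreters

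*Protocol article*

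**What the plan says.** All places are in the protocol article.

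- **Who will be blinded {24a}**, on the period after export: "Afterwards, the data is processed, analysed, and interpreted by blinded data managers, statisticians, junior researchers, and conclusion makers". The stated safeguard is that an unblinded data manager recodes the conditions at export, and that this is reversed only once conclusions have been drafted. The section then says that this procedure secures the blinding of statisticians and conclusion makers. It closes with: "The junior researchers are not blinded during data collection to enable effective day-to-day management of the trial".
- **Roles and tools of sequence generation {21a}**: randomisation is "performed through the fully automated web-based electronic data capture system of CASTOR EDC by the two unblinded junior researchers".
- **Allocation concealment mechanism {22}**: "randomisation can only be performed by the junior researchers and the outcome remains concealed to all blinded research assistants".
- **Implementation {23}**: "junior researchers responsible for executing treatment allocation are blind to the future order of assignments".
- **Data Management {26}**: "In all data files and during statistical analysis, participants are identified through their study ID". On export rights: "Only the junior researchers and the data manager are permitted to export data". The same section also says that exported data are made anonymous before they are stored and analysed.

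**The concern.** Section {24a} gives the junior researchers two incompatible descriptions. They are unblinded during the trial, and they are blinded when they process, analyse and interpret its results. Someone who has executed and managed individual allocations does not become blind because the arm variable is given a neutral name, least of all when records keep the identifier used throughout the trial.

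At stake is how much credit a reader may give to the blinded analysis. Masking labels until conclusions are drafted is meant to keep preference for a result out of data processing and interpretation. If two people in that process can read the arms, the protection fails for their part of it. It then depends on their not sharing what they know with the colleagues who are masked.

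**Working it through.** No arithmetic applies; the point is about roles and access. Set side by side, the sections give this chain.

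1. **Who knows the allocations?** Sections {21a} and {22} make the two junior researchers the only people who randomise. The outcome is concealed from the blinded research assistants, not from them. Section {23} blinds them only to assignments still to come, so allocations already made are known to them. The description of the steering committee {3d} also gives them day-to-day execution of the trial and a seat on that committee. Under {15b}, the committee discusses proposed changes of treatment and cross-overs. If recruitment reaches the plan, they will have executed all 358 allocations.

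2. **Under which identifier?** Section {33} says a study ID is generated after consent for data collection in CASTOR EDC. Section {23} says each participant has a file there and is randomised there. It follows, very probably, that the junior researchers see each allocation against its study ID. No sentence says this outright, so it is an inference, though a strong one.

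3. **Does the identifier survive into analysis?** Section {26} says participants are identified by study ID in every data file and during analysis. Its statement that exported data are made anonymous could mean that IDs are dropped, but that would contradict the sentence on study IDs in the same section. The two statements need reconciling.

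4. **Does recoding the arm label mask someone who knows the pairs?** Call the masked arms A and B. If one participant in arm A is known to have been allocated to GIT-PD, then A is GIT-PD and B is specialist treatment for every record. One remembered or looked-up pair is enough.

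5. **Is access to such a pair restricted?** Section {26} gives the junior researchers export rights of their own, whereas the safeguard in {24a} rests on the data manager recoding at export. The document does not say that their exports are limited to masked data.

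6. **Who remains masked?** Nothing in the document shows that the statisticians or conclusion makers see allocations. For them, steps 1 and 2 do not apply, and recoded labels work as long as nobody gives them the key.

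The claimed blinding therefore fails for the junior researchers, and the document does not show it failing for statisticians or conclusion makers.

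**The case against.** The strongest reply is that {24a} does not really promise blinding for the junior researchers. Its assurance names only statisticians and conclusion makers, and the section openly says the junior researchers are unblinded during data collection. This is a fair account of those sentences. It does not remove the contradiction, because the list in the same section still calls the junior researchers blinded at analysis and interpretation, and disclosing the first state does not make the second true.

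A reader might infer several stronger points that the document does not support:

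- **That there is no blinded analysis at all.** The masking procedure is workable for the other roles, and the blinded STiP-5.1 assessment, which is the protection from bias that the article argues for at most length, is a separate matter.
- **That treatment minutes and duration would reveal the arms in the primary analysis.** These are collected {15c} and used for costing {27a}, but no section places them in the primary-analysis file, and the primary model takes no covariates beyond the baseline outcome value.
- **That knowledge of the arms would steer every analysis choice.** The switch to a one-sided interval is triggered by an enrolment shortfall, which does not depend on the arms. The convergence fallbacks are listed in advance, and the per-protocol analysis is only supportive {27b}. Some judgement remains, since the fallbacks are offered as alternatives and {27b} gives no threshold for dropping out of treatment, but it is limited.

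Section {26} also provides automated transformation scripts and a full audit trail, exports included. These make interference easier to detect. They do not restore blinding.

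**Conclusion.** The point holds for one role. The two junior researchers cannot be described as blinded analysts or interpreters, because they execute every allocation, are unblinded during data collection, may export data, and would work with files that keep the study ID. Recoding a two-arm label does not mask them.

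The size of any bias cannot be derived from the document, and counting the allocations they execute does not measure it. The conclusion rests on two assumptions: that allocations in CASTOR EDC are visible to the junior researchers against the study ID, and that the sentence keeping study IDs during analysis prevails over the wording on anonymisation. If IDs were in fact removed or replaced before analysis, and the junior researchers had no route back to them, the problem would be much smaller, but the list in {24a} would still need to explain how people unblinded throughout the trial become blinded.

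This is worth correcting before analysis begins. It is no ground for discounting the masked work of the statisticians and conclusion makers.

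**What to change.** Choose one of two routes.

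1. In {24a}, remove the junior researchers from the list of blinded people, and state that they take no part in analysing or interpreting the primary outcomes until conclusions are drafted.
2. Have the unblinded data manager replace the study IDs with a new random key before the masked dataset is released, and in {26} restrict export of that dataset to the data manager. Treatment site must stay in the file, because it is the third level of the primary model.

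The first route is cleaner. The second reduces the risk but may not remove it, since anyone holding data under the study IDs could try to match records on their values.

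Either way, reconcile {21a}, {24a} and {26}, including what being made anonymous means when study IDs are used during analysis. It would also help to state that the allocation key must not be shared with masked colleagues.

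The cost is a few changed sentences. Under the first route the junior researchers join the primary analysis and write-up later; under the second, one re-keying script is needed. Recruitment, sample size and participants are unaffected.
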